## Abstract

**Background:**

Primary insomnia (PI), commonly identified by difficulties in initiating and maintaining sleep, negatively impacts both physical and mental health and increases the risk of occupational and vehicular accidents. Previous research has indicated that shallow needling, a form of acupuncture, may ameliorate the symptoms of PI. Nevertheless, the scientific evidence regarding its efficacy in enhancing sleep quality remains limited.

**Objective:**

This trial aims to assess the therapeutic efficacy of shallow needling in the treatment of chronic PI in adults.

**Methods:**

A single-center, prospective, assessor-blinded randomized controlled clinical trial retrospectively registered with the International Traditional Medicine Clinical Trial Registry (ITMCTR2024000409). With 2 parallel arms, the trial will be conducted at the Affiliated People’s Hospital of Fujian University of Traditional Chinese Medicine. A total of 124 participants with PI will be randomly divided into the control group and the treatment group in a ratio of 1:1 (n=62 for each group). The control group will receive 1 mg eszopiclone orally, once a day for 4 weeks. In addition to taking eszopiclone, the treatment group will receive shallow needling therapy once daily, 5 times a week, for 4 weeks. Data will be collected at 3 time slots—before treatment, after treatment, and 4 weeks after treatment—and will be analyzed using SPSS (version 23.0). The primary outcome measure is the Pittsburgh Sleep Quality Index. The secondary outcome measures include the Hamilton Anxiety Scale, Insomnia Severity Index, serum neurotransmitter detection (including dopamine, norepinephrine, and melatonin), sleep parameters, and magnetic resonance spectroscopy of the thalamus.

**Results:**

Participant recruitment for this study is currently in progress. The first participant was enrolled in August 2023, marking the official commencement of the trial. Following the completion of recruitment, data processing and statistical analysis will be initiated. The final results of this study are expected to be prepared and submitted for publication in January 2026.

**Conclusions:**

This study will evaluate the therapeutic effectiveness and safety of shallow needling in the treatment of chronic insomnia to provide the necessary scientific basis for the clinical application and promotion of shallow needling. The findings of this study may provide a scientific and standardized treatment protocol for shallow needling in adults with chronic insomnia.

## Introduction

Insomnia is one of the most common sleep disorders globally, characterized by difficulty in falling and staying asleep, early morning awakenings, and an inability to return to sleep [1]. It may occur secondary to psychiatric or organic disorders, the use of prescribed or illicit substances, alcohol consumption, or a combination of these factors. However, insomnia can also occur independently, known as primary insomnia (PI), which is driven by a psychophysiological hyperarousal process [2]. A recent large-scale study revealed that approximately 16.2% of adults worldwide experience insomnia [3], with PI accounting for an estimated 25% of the cases. Notably, many of these patients experience a chronic course of the disorder [4]. Chronic insomnia has been associated with a wide range of adverse health outcomes, including headaches, dizziness, hypertension, and various cardiovascular and cerebrovascular diseases, which collectively undermine physical health, reduce quality of life, and pose significant risks to public safety. These effects result in substantial harm to both individuals and society [5,6]. Therefore, chronic PI has become a critical public health issue in contemporary society.

Sedative drugs and cognitive behavioral therapy (CBT) are the primary interventions for insomnia [7]. Although sedative drugs have a fast onset of action, their adverse effects with long-term use are notable, including persistent sleep difficulties, performance issues, memory disorders, driving accidents, and withdrawal syndrome [8]. In contrast, CBT is widely recognized as the first-line treatment for chronic insomnia by recognized organizations, including the American College of Physicians [9], the American Academy of Sleep Medicine [10], and the European Sleep Research Society [7]. Despite its effectiveness for insomnia, CBT is not commonly used due to the intensive labor required and high costs, which may lead to low patient compliance [11]. Given these limitations, it is crucial to seek additional safe and effective nonpharmacological treatments to optimize existing therapies for chronic insomnia.

As an important component of traditional nondrug therapy, acupuncture has long been used for the treatment of insomnia in China [12] [1]. In recent years, a growing body of evidence-based research has reported the effectiveness and feasibility of acupuncture therapy in improving sleep quality [13-16]. However, in clinical practice, the discomfort and pain associated with traditional acupuncture often cause significant distress and fear among patients, which limits its widespread acceptance. Therefore, the development of noninvasive and painless acupuncture techniques has become a key focus of research in this field.

Shallow needling, a special type of acupuncture, is derived from the *hammer needle* in the ancient system of 9 needles. The nationally famous senior traditional Chinese medicine experts, [name] and [name], have inherited and innovated this therapy, developing it into a characteristic acupuncture method of Fujian province [17]. In 2019, it was listed as part of the sixth batch of intangible cultural heritage projects in Fujian province and was selected as a characteristic traditional Chinese medicine technique by the National Administration of Traditional Chinese Medicine. Shallow needling is a noninvasive technique in which a rounded needle tip rests on the skin surface without penetrating it. Compared to conventional acupuncture needles, the needles used in shallow needling are designed with a thicker body, a longer handle to facilitate scraping with the fingernail, and a rounded tip that rests on the skin surface, avoiding penetration and minimizing discomfort (Figure 1). The technique involves applying a scraping motion with the fingernail on the needle handle at specific acupoints on the body surface to produce a needle sensation. This method promotes the flow of meridian Qi and blood, regulates the internal balance of the body, and treats various diseases.

**Figure 1. F1:**
[figure not shown]
Structure of the shallow needle used in this study, illustrating the key components, including the needle tip, body, root, handle, and tail.

As a noninvasive and painless alternative, shallow needling is an attractive option for patients seeking less discomfort during treatment. Although shallow needling shows promising potential, its clinical efficacy in treating insomnia has not been thoroughly explored. A recent systematic review and meta-analysis [18] demonstrated that compared to nonshallow needling treatments, shallow needling demonstrates greater efficacy in reducing Pittsburgh Sleep Quality Index (PSQI) scores and improving clinical efficacy rates. However, most studies have small sample sizes, unclear reporting, and potential bias risks, and there is still insufficient high-quality clinical evidence to support its effectiveness.

Furthermore, the specific mechanisms through which shallow needling ameliorates insomnia remain poorly understood, which has limited its broader clinical application. The current understanding of PI pathogenesis centers on hyperarousal as a core neurobiological pathology. Patients exhibit persistent whole-brain hyperexcitability, characterized by increased beta-band electroencephalographic activity. This abnormal cortical excitation interacts with the hypothalamic-pituitary-adrenal axis hyperactivity and autonomic nervous dysfunction, contributing to a vicious cycle of insomnia [19].

Existing evidence indicates that shallow needling restores autonomic balance [20] and mitigates the hypothalamic-pituitary-adrenal axis dysfunction, alleviating insomnia symptoms through correcting neuroendocrine abnormalities [21]. However, mechanistic research on the central nervous system effects of shallow needling remains inadequate, particularly regarding its impact on key brain regions regulating the sleep-wake cycle. Although preliminary studies have shown that shallow needling can regulate the functional connectivity of emotion-related brain circuits in patients with PI [22] and reduce the beta wave power in the frontal lobe and central regions of the brain [23], thereby creating neural conditions for sleep initiation, these findings still fail to systematically explain their core action targets.

The thalamus is a critical brain region involved in the regulation of sleep and wakefulness, and it plays a key role in sensory integration [24]. Neuroimaging studies have demonstrated that alterations in thalamic activity are associated with sleep disorders, including insomnia [25]. Recently, acupuncture has been shown to regulate the functional connections between the thalamus and the emotional network in patients with insomnia and improve the state of excessive arousal. Nevertheless, the underlying metabolic mechanisms remain unclear. Accumulating research has demonstrated that the occurrence of PI is closely linked to abnormal brain metabolites. Specifically, γ-aminobutyric acid (GABA) and glutamate/glutamine (Glx) maintain the balance between excitatory and inhibitory signals and are thought to be key players in sleep regulation. Notably, reduced GABA levels have been linked to hyperarousal in patients with insomnia, while abnormal Glx activity may contribute to disrupted sleep patterns [26]. Magnetic resonance spectroscopy (MRS) offers a noninvasive approach to quantify the concentrations of neurochemical substances within specific brain regions of living participants [27], providing a valuable tool for exploring the neurophysiological effects of acupuncture.

Therefore, we conducted a randomized controlled trial with a larger sample size and a rigorous design to generate high-quality clinical evidence regarding the efficacy of shallow needling for insomnia. We hypothesized that shallow needling acts as an effective external stimulus that modulates thalamic neurochemical activity through sensory nerve afferent pathways. To comprehensively evaluate its therapeutic effects, we incorporated peripheral serum neurotransmitter assays and objective polysomnographic sleep architecture measures, aiming to further elucidate the neural mechanism through which shallow needling ameliorates chronic PI.

## Methods

### Research Objectives

The purpose of this study is to evaluate the efficacy and safety of shallow needling in the treatment of chronic insomnia. The results of this study may provide a noninvasive and painless alternative therapy for patients with chronic insomnia.

### Hypotheses

We hypothesize the following:

Compared with the control group, the symptoms of insomnia and anxiety in the treatment group were significantly relieved after treatment according to the scale evaluation. At the same time, according to the objective sleep outcome test results, the sleep treatment of the treatment group was further proved to be improved.Compared with the control group, the levels of serum neurotransmitters, central neurotransmitters, and metabolites in the treatment group were significantly improved, reflecting the better regulatory effect of shallow needling.

### Ethical Considerations

This study protocol has been approved by the ethics committee of the Affiliated People’s Hospital of Fujian University of Traditional Chinese Medicine (IRB 2023-014-02). All patients and participants will provide written informed consent before their participation in this study. To protect participants’ privacy and personal information in compliance with international ethical guidelines (eg, the World Medical Association Declaration of Helsinki), all identifiable data will undergo strict deidentification and anonymization processes immediately after data collection. This ensures that no individual participant can be traced or identified during data analysis, storage, or reporting stages. In recognition of participants’ time and travel costs incurred during the study, each participant will receive a one-time transportation subsidy of 450 CNY (approximately US $63). The subsidy is provided to offset travel expenses related to study visits and will be distributed upon completion of all required study procedures.

### Study Design

This study design is a prospective, randomized controlled trial with 2 parallel arms. The trial was retrospectively registered with the International Traditional Medicine Clinical Trial Registry under the number ITMCTR2024000409. The delay in registration occurred because the research team prioritized obtaining ethical approval and completing preliminary clinical preparations to ensure participant safety and study quality in the early stage; the registration process was initiated and completed immediately after the above preparatory work and subsequent administrative clearance were finalized. This protocol follows the guidelines of the Standard Protocol Items: Recommendations for Interventional Trials (SPIRIT) (Checklist 1). We will compare the differences between shallow needling and pharmacotherapy for chronic PI in adults. The study procedure and details are presented in Figures2  3.

**Figure 2. F2:**
[figure not shown]
Flow diagram of the trial. DA: dopamine; MT: melatonin; NE: norepinephrine.

**Figure 3. F3:**
[figure not shown]
Study schedule of enrollment, interventions, and assessments. HAMA: Hamilton Anxiety Scale; ISI: Insomnia Severity Index; MRS: magnetic resonance spectroscopy; PSQI: Pittsburgh Sleep Quality Index.

### Participants

#### Sample Size

According to the relevant literature [28], the overall efficacy rate for the control group is reported to be 79.48%, whereas the treatment group is expected to have an efficacy rate of 98%. Assuming a significance level (α) of 0.05 and a power (1-β) of 0.9, the sample size was calculated using PASS 15.0 software. A minimum of 56 participants is initially required for each group. Considering a 10% dropout rate, we plan to recruit at least 62 participants per group. Therefore, a total of 124 participants are needed for this study.

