### Outcome Measures

#### Primary Outcome Measures

PSQI [29] is a questionnaire used to assess an individual’s sleep quality, with good reliability and validity, indicated by a Cronbach α coefficient of 0.83 and a test-retest reliability of 0.85 [30]. It consists of 7 components: subjective sleep quality, sleep latency, sleep duration, habitual sleep efficiency, sleep disturbances, use of sleeping medication, and daytime dysfunction. The total score ranges from 0 to 21. A global PSQI score greater than 7 indicates the presence of sleep disorders, with higher scores reflecting poorer sleep quality. PSQI will be assessed before treatment, after treatment, and 4 weeks after treatment completion (follow-up).

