### Statistical Analysis

In this study, data will be analyzed with SPSS (version 23.0) software. Continuous variables will be reported as means and SDs, and categorical variables will be presented as frequencies or percentages. To compare continuous variables between the 2 groups, normality and homogeneity of variance will be initially evaluated. If these assumptions are satisfied, a 2-tailed *t* test will be used. Otherwise, a nonparametric rank-sum test will be used. Categorical variables will be analyzed using the chi-square test or Fisher exact test. *P* values of .05 or less will be considered statistically significant.

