Although our study comprehensively evaluates the efficacy of shallow needling for chronic PI, there are several limitations to consider. First, due to funding constraints, this study was designed as a single-center trial with a relatively limited sample size, which may, to some extent, affect the generalizability of the findings. Moreover, the assumed between-group difference used in the sample size calculation may have been overly optimistic, resulting in insufficient statistical power to detect more subtle yet clinically meaningful effects of shallow needling. Nevertheless, our study offers a valuable foundation for understanding the efficacy of shallow needling, and we hope that future large-scale, multicenter studies will further validate and extend these findings, thereby strengthening the evidence base for this intervention. Second, all participants received baseline pharmacotherapy with eszopiclone for ethical and adherence reasons, which may introduce confounding effects when interpreting the specific contribution of shallow needling. Therefore, we incorporated a follow-up period to reduce the residual pharmacological effects and more accurately assess the long-term efficacy attributable to shallow needling therapy. Finally, given the unique characteristics of shallow needling, developing a sham intervention that is both physiologically inert and indistinguishable from the actual treatment is difficult. Any form of simulated contact or scraping may inadvertently induce physiological reactions, thereby compromising its validity as a true placebo. Therefore, we adopted multidimensional objective outcome measures and blinded the evaluators and statisticians to reduce potential bias risks. At the same time, a 4-week follow-up was conducted to reduce the short-term placebo effect and enhance the validity of the research results. We hope that future research can develop and apply innovative sham-control methods tailored to shallow needling techniques to further reduce the possible placebo bias.

To the best of our knowledge, this is the first randomized controlled trial to objectively assess the efficacy of shallow needling for the treatment of insomnia and provide new insights into its neurophysiological mechanisms. The results of this study will establish a basis for the wider use of shallow needling in clinical practice and provide fresh evidence-based support for its application in treating insomnia.

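### The stated 90% power belongs to a binary efficacy rate that is not a listed outcome, so it does not apply to the primary outcome, the PSQI score

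*Protocol article*

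**What the plan says.** The Sample Size section of the protocol article takes its inputs from one cited source: "the overall efficacy rate for the control group is reported to be 79.48" percent, "whereas the treatment group is expected to have an efficacy rate of 98" percent. It continues: "Assuming a significance level (α) of 0.05 and a power (1-β) of 0.9". The result is "A minimum of 56 participants is initially required for each group", raised to 62 per group for 10% dropout, 124 in total. No other basis for the sample size is given.

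The Methods part of the abstract states: "The primary outcome measure is the Pittsburgh Sleep Quality Index". The Primary Outcome Measures section describes the PSQI as a score ("The total score ranges from 0 to 21") and gives no responder definition. The Secondary Outcome Measures section and its subsections cover the Hamilton Anxiety Scale, the Insomnia Severity Index, polysomnography, serum neurotransmitters and thalamic spectroscopy. No efficacy rate is among them.

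For continuous variables, the Statistical Analysis section says that, where assumptions hold, "a 2-tailed *t* test will be used", and otherwise a rank-sum test. The limitations paragraph of the Discussion concedes that "the assumed between-group difference used in the sample size calculation may have been overly optimistic".

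**The concern.** A power statement holds for one endpoint, one test and one assumed effect. Here the endpoint of the calculation is a proportion and the primary outcome is a score, and nothing in the article connects the two. No PSQI difference or SD is assumed anywhere, so the 90% is attached to a comparison that is not among the trial's stated outcomes.

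What is at stake is how the primary result will be read. A reader who takes the 90% as the power of the PSQI comparison has no basis for doing so, whether the result is positive or null, and cannot tell from the article which PSQI difference the trial was able to detect.

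**Working it through.** **Inputs from the article.** Control rate p1 = 0.7948, treatment rate p2 = 0.98, alpha 0.05, power 0.90, 56 per group, 10% dropout, 62 per group (Sample Size); allocation 1:1 (Randomization); two-tailed t test (Statistical Analysis). The Sample Size section does not say whether alpha is one- or two-sided; two-sided is used here, in line with the t test.

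**Step 1: reproduce the stated 56.** Two independent proportions, normal approximation, unpooled variance:

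n = [p1(1−p1) + p2(1−p2)] × (z0.975 + z0.90)² / (p2 − p1)²

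- p1(1−p1) + p2(1−p2) = 0.1631 + 0.0196 = 0.1827
- (1.960 + 1.2816)² = 10.507
- (0.98 − 0.7948)² = 0.1852² = 0.03430
- n = 0.1827 × 10.507 / 0.03430 = 55.97, rounded up to 56

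This matches the article. Then 56 × 1.10 = 61.6, rounded up to 62, and 2 × 62 = 124. The calculation is therefore a two-proportion one, and its arithmetic is sound for that endpoint.

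**Step 2: what 56 or 62 per group gives for a score.** For a two-sided 5% t test, the standardised difference d with 90% power is, to a normal approximation, d = (1.960 + 1.2816) × √(2/n). For n = 56 this is 3.2415 × 0.1890 = 0.613. With the noncentral t distribution it is 0.618 for 56 per group and 0.587 for 62 per group, that is, about 0.62 and 0.59.

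**Step 3: translate into PSQI points.** The article gives no SD, so SDs of 2, 3 and 4 points are assumptions. With 56 per group:

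| Assumed SD | Difference with 90% power | Power for 1 point | Power for 2 points |
|---|---|---|---|
| 2 | 0.618 × 2 = 1.2 | 75% | above 99% |
| 3 | 0.618 × 3 = 1.9 | 42% | 94% |
| 4 | 0.618 × 4 = 2.5 | 26% | 75% |

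Over this grid, power runs from 26% to above 99%. The stated 90% lies inside that range, and nothing in the article narrows it.

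**The case against.** The strongest reply is that the efficacy rate may be a responder rate defined on PSQI reduction in the cited source, so that it is a dichotomised form of the same instrument. That cannot be excluded, but the article does not say so. Its Introduction, describing a different source, reports PSQI scores and clinical efficacy rates as two separate results. Even if the rate did come from the PSQI, comparing proportions and comparing scores have different power, and the rate would still not be a listed outcome. What stands is that the rate should be called undefined and unlinked to the PSQI, not shown to be unrelated to it.

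A second reply is that the Discussion already warns about power. It does, but only because the assumed difference may be too large. It does not say that the calculation concerns another endpoint. The warning does weaken any suggestion that readers are left with an unqualified 90%.

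A third is that a fuller protocol or analysis plan may cover the matter. The point is not an omission, however: the article states a basis for power and a primary outcome that do not match, and a document not shown cannot make this 90% apply to the score.

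A reader might infer that the trial is underpowered for the PSQI. The article does not support that. The true difference and SD are unknown, and for a 2-point difference power exceeds 90% at an SD of 2 or 3. As an illustration on an unstated assumption, if the rates came from cutting a roughly normal score, 79.48% against 98% would correspond to z0.98 − z0.7948 = 2.054 − 0.823 = 1.23 SD, about twice the 0.62 needed. The direction of the discrepancy is therefore open.

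**Conclusion.** The point holds as a mismatch of endpoints. The 90% power and the 56 per group belong to a comparison of 79.48% with 98% on a rate that is neither defined nor listed as an outcome. They do not describe the primary comparison, which is on a 0 to 21 score. PSQI power cannot be derived from the article. The most that can be said is that 56 evaluable per group give 90% power for about 0.62 SD, and 62 per group for about 0.59 SD. This rests on a two-sided 5% t test with equal groups; the values in points rest on assumed SDs. If the rank-sum test is used instead, the figures are only a guide. Nothing here shows that N is too small or that the arithmetic is wrong.

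**What to change.** Keep N = 124, and keep the efficacy-rate calculation as the record of how N was set. Then change the text of the Sample Size section as follows:

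- State that this calculation does not give the power for the PSQI.
- Add that a two-sided 5% t test has 90% power for a standardised PSQI difference of about 0.62 with 56 evaluable per group (0.59 with 62), at the time point named as primary.
- Translate that into points with an SD taken from a cited source, for the same quantity that will be analysed (score or change). For orientation, it is about 1.2, 1.9 or 2.5 points at assumed SDs of 2, 3 or 4.
- If an efficacy rate is reported, label it as not prespecified as an outcome.

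The cost is a text change with no extra participants. The downside is that 90% power is no longer claimed for the primary outcome. The detectable difference is also being stated late: the Results section reports 120 participants enrolled by April 2025, so the text should disclose that the statement was added after most of the 124 had been recruited and did not determine N.
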